### Participants

The initial identification of suitable participants with MCI and mild dementia will take place at various sites within the province of Zamora, Spain: community centres, memory clinics, public hospitals, daycare centres and residential centres.

The inclusion criteria for participants with MCI and mild dementia will be: aged over 60 years, possess the capacity for making decisions, have a reference person or a caregiver, and be able to read and write in Spanish. For those with a diagnosis of MCI, the study will comply with the criteria of Petersen [32] and the International Working Group (IWG) for people with amnestic MCI [33], where participants should have a Clinical Dementia Rating (CDR) score = .5 and Geriatric Depression Scale (GDS) < 5. For those with a diagnosis of dementia, participants should meet *the Diagnostic and Statistical Manual for Mental Disorders* (DSM-5) diagnostic criteria for major neurocognitive disorders, CDR score ≥ 1 and < 2 and GDS score < 5 [34].

The exclusion criteria for both groups will be: loss of senses that make it difficult to use the devices (blindness, deafness) or severe physical comorbidity (a disease causing tremor), current significant neurological disease (e.g. Parkinson’s disease, Huntington’s disease, Lewy-body dementia, epilepsy, multiple sclerosis, traumatic brain injury, etc.), current significant anxiety or depressive disorder (DSM-5 criteria) that would affect cognitive functioning and thus act as confounders, having a current history of alcoholism and/or substance abuse (including alcohol-related dementia), or currently taking any antipsychotic medications. All participants must be willing to participate in the study voluntarily and will sign an informed consent form. Some of the participants may be taking anticholinesterase inhibitors or memantine. These participants must have been stabilised on their current dose for a minimum of 1 month prior to the baseline assessment. This is to ensure that any changes will not be confounded by medication effects. All inclusion/exclusion criteria are summarised in Table 1.

**Table 1 Tab1:** Inclusion/exclusion criteria

	MCI	PwD
Inclusion criteria	Age 60 + years Reference person Reads and writes in Spanish Petersen criteria (1999) for PwaMCI: (1) memory problems, (2) objective memory disorder, (3) absence of other cognitive disorders or repercussions on daily life, (4) normal general cognitive function and (5) absence of dementia CDR = .5 GDS < 5 MMSE ≤ 27	Age 60 + years Reference person Reads and writes in Spanish DSM-5 criteria for mayor neurocognitive disorder: A. Evidence of significant cognitive decline from a previous level of performance in one or more cognitive domains: complex attention, executive function, learning and memory, language, perceptual-motor, social cognition. (1) Concern of the individual, a knowledgeable informant or clinician that there has been a significant decline in cognitive function, (2) A substantial impairment in cognitive performance documented by standardised neuropsychological testing B. The cognitive deficits interfere with independence in everyday activities. At a minimum, assistance should be required with complex instrumental activities of daily living, such as paying bills or managing medications C. The cognitive deficits do not occur exclusively in the context of a delirium D. The cognitive deficits are not better explained by another mental disorder, with or without behavioural disturbance (e.g. major depressive disorder, schizophrenia) CDR ≥ 1 and < 2 GDS < 5 MMSE 20 < x < 25
Exclusion criteria	Loss of senses Severe physical comorbidity Current significant neurological disorder Current significant anxiety or depressive disorder History of alcoholism and/or substance abuse Current antipsychotic medication and/or cognition-affecting medication Recent hospitalisation for mental illness or stroke (in the past 6 months)	Loss of senses Severe physical comorbidity Current significant neurological disorder Current significant anxiety or depressive disorder History of alcoholism and/or substance abuse Current antipsychotic medication and/or cognition affecting-medication Recent hospitalisation for mental illness or stroke (in the past 6 months)

*MCI* mild cognitive impairment, *PwD* people with dementia

An additional criterion will be MMSE score, defined by a cut-off point of ≤ 27 points for MCI and 20 < x < 25 points for people with mild dementia. The score of each participant in this test will be adjusted according to their age and years of education based on the study by Blesa, Pujol and Aguilar [35] as follows: (1) for participants between 51 and 75 years of age and 8 or less years of education + 1 point, and − 1 point for more than 17 years of education; (2) for participants over 75 years of age and 8 or less years of education + 2 points, and + 1 point for 9–17 years of education.

### Allocation and randomisation

Participants will be randomly allocated in a 1:1:1:1 ratio to either of the four trial arms using a computer-generated random number sequence. The Epidat 4.1 programme will be used to generate this sequence. The allocation will be carried out by an independent researcher who will be unaware of the characteristics of the study. Participants will be allocated to each group using simple randomisation. Simple randomisation will allocate every participant randomly in a group independently of their characteristics (age, sex, education, area, etc.).

Participants will agree to participate before the random allocation takes place and without knowing to which group they will be allocated. The staff member responsible for sequence generation will provide participants with the details of the treatment group that they were allocated to independently from study coordinators. Participants will receive a sealed envelope by post with sufficient details and instructions about how to start their participation in the treatment.

### Procedure and intervention

#### Usability study

The techniques used to carry out the usability study will be: focus group, users’ testing and usability questionnaires.

The usability study will consist of three different phases:Pre-experimental phase

### Focus group

Focus group of GRADIOR: this will be used to determine whether the experience of using the program is adequate and if its interface is functional and intuitive for people with MCI and mild dementia, as well as for the healthcare professionals. The following participants will be recruited: two groups with MCI, two groups with mild dementia and two groups of professionals who have experience with GRADIOR in PwD and/or MCI.

Focus group of ehcoBUTLER: this will be used to determine whether the characteristics and tools of the ehcoBUTLER platform, as well as its design, would be well accepted by people with MCI and mild dementia, as well as by relatives and professionals. Participants will be shown a video about the programme and its tools. The following participants will be recruited: two groups with MCI, two groups with mild dementia, two groups of informal carers or family members and two groups of professionals who have worked or work with PwD and/or MCI.

The different focus groups of both GRADIOR and ehcoBUTLER will consist of five to six people each. In order to carry out focus groups, scripts with general and specific open questions will be developed to obtain the necessary information for the research. In addition, participants will obtain an informed consent to record the sessions in audio and video for later analysis.

### Users’ testing

This will be carried out in a usability laboratory and users’ interactions with the GRADIOR and ehcoBUTLER programs will be recorded.

GRADIOR user test: five people with MCI, five with mild dementia and five professionals will be recruited who have no prior experience with GRADIOR.

ehcoBUTLER user test: five people with MCI, five people mild dementia and five professionals will be recruited.

In both cases, the users will perform a series of practical tasks in the GRADIOR and ehcoBUTLER programs.

Only one user at a time can perform the experiment in order to establish a careful monitoring of their actions and behaviour; measures of effectiveness, efficiency and satisfaction. In addition, the session will be recorded in audio and video for later analysis. All participants should have some prior experience with information and communication technology (ICT). Before starting the tests, participants will be asked to sign an informed consent. At the end of the assignment the participants will have to complete the System Usability Scale (SUS), which will serve to assess the usability and satisfaction with the programs.2.Experimental phase

During this phase, data in the RCT will be collected from the participants using GRADIOR and/or ehcoBUTLER about all the incidents that occurred with the GRADIOR and ehcoBUTLER programs for further analysis. All the incidents that arise during the treatment about technical aspects and use of the program, referring to both the software and hardware, will also be collected. These will be reported on a record sheet. This data will be analysed and will serve to assess the problems encountered by users and the difficulties of implementing the program.3.Post-experimental phase

Once the experiment is finished, the User Experience Questionnaire (UEQ) will be administered, which will serve to assess the participants’ user experience.

### Intervention

Intervention sites will vary depending on accessibility and mobility of participants. Community centres, social care centres, memory clinics, community centres, residential care homes and similar facilities within the province will participate in the study.

The first cognitive rehabilitation session with GRADIOR will be used as a baseline which will help determine each participant’s level of ability. The baseline treatment is a shorter version of the usual intervention and includes exercises from various subdomains which will determine the level of difficulty for the main treatment and also help the participants to familiarise themselves with the programme and its interface. During the first psychosocial stimulation session with ehcoBUTLER, a member of staff will create a user profile for each participant and demonstrate how to use the platform.

#### GRADIOR: Computer-based cognitive rehabilitation (GRA)

GRADIOR is a neuropsychological rehabilitation programme activating seven areas of cognitive functions (memory, attention, orientation, perception, calculus, executive functioning and reasoning) with specific tasks. In total, GRADIOR contains 48 different types of exercises with 2 to 11 levels of difficulty (see Appendix). For every participant, the GRADIOR treatment will include exercises for all cognitive subdomains. At the starting point of the treatment, all the participants will receive the same set of exercises which will differ in the level of difficulty for every subdomain based on the participant’s performance in the preliminary baseline treatment.

Participants will attend treatment sessions three to four times per week for 30 min per session. The days or distribution of treatment sessions during the week will depend on the availability of each centre and on the individual availability of participants. The treatment for each participant will be adjusted after 4 months when a midterm assessment will take place. The treatment can also potentially be adjusted before this time based on the participant’s performance in the exercises.

Every exercise in GRADIOR has a duration of 1 min during which different stimuli are presented to the participant who is then asked to provide a specific response (e.g. point only to a certain group of objects). During one treatment session, the exercises are randomised for each subdomain; however, the order of the subdomains in the treatment is fixed. If the participant does not complete all exercises on the list in one session, the subsequent session will pick up from where they stopped, i.e. with tasks for subdomains which are next on the list. In this way, the programme continues in a loop. The user does not repeat the same exercises every session, but only once they have finished the previous set.

#### ehcoBUTLER: Computer-based psychosocial stimulation (PSS)

EhcoBUTLER is an e-health platform available via the Internet, which aims to promote physical and mental health, social participation, quality of life and personal wellbeing. EhcoBUTLER is aimed at people with MCI or mild dementia as well as their carers.

During the first two sessions participants will be trained to use the system, after which they will use the platform for 5 h per week or more. The time schedule of usage of the platform will depend on each participant and their needs and individual availability. It will be recommended to participants that they use the platform for 2 h per day. To ensure correct usage of the platform, the sessions taking place outside of the participants’ homes will be facilitated by a member of staff. Study coordinators will have access to the data registered by the platform to ensure the participation of all users. On the other hand, the therapist may use the ‘Task List’ function to propose activities to the participants and subsequently monitor their accomplishments.

#### ehcoBUTLER CARE: Combined treatment (GRADIOR + psychosocial stimulation) (COM)

The group receiving both cognitive rehabilitation and the psychosocial stimulation treatment will have scheduled sessions with GRADIOR twice per week for 30 min per session and will be advised to use ehcoBUTLER for at least 3 h per week. The treatment sessions with GRADIOR will be the same as the group only using GRADIOR and the same procedure will be followed to determine the baseline, adjustments of treatments and levels of difficulty.

#### Treatment as usual

Treatment as usual (TAU) is defined as individual care depending on each participant’s needs, including medication, social activities, etc. which will not be influenced by study coordinators or other staff members included in the study. TAU is usually region-specific due to influences in a person’s access to services and treatment availability. Therefore, the outcomes of care for these participants may vary. Any cognitive intervention, psychosocial stimulation programmes or activities will be recorded as potential influences on the outcome measures. Participants in this group will be put on a waiting list for the cognitive rehabilitation treatment with GRADIOR and ehcoBUTLER, and will be offered these treatment choices once the main trial is finished. TAU is usually also available to participants in the active treatment groups.

### Interventions – modifications

The intermediate testing of cognitive functions, screening, quality of life and evaluation of emotional state scheduled after 4 months will provide additional data for treatment modifications. These tests are important in case of a scenario where there is a lack of efficacy of the treatment, observed harms or changes in physical health with an impact on cognition and emotions, or for any other relevant reason.

### Treatment adherence

Interviewers will be trained clinical psychologists or neuropsychologists. All interviewers and staff included in the study will be provided with a set of guidelines for communication with participants to ensure that they have a correct understanding of the treatment sessions and that effective communication is established between participants and all staff members. During all GRADIOR treatment sessions, a member of staff will be present to provide support to participants, enabling their full participation in the treatment. However, the member of staff will not interfere with the treatment. All participants will be given contact details and times when they can contact study coordinators regarding any difficulties experienced or if questions arise during the treatment.

The sessions for both groups receiving cognitive rehabilitation treatment (GRADIOR and ehcoBUTLER CARE or combined treatment) will be managed by two study coordinators independently in each group to avoid personal bias. The treatment coordinators are trained in advanced in how to use the GRADIOR programme, including setting up and adjusting treatments, and also have a degree in psychology. Participants receiving treatment in a group setting will be supported during each session by a separate staff member independent from the treatment coordinators.

To ensure a high number of participants finish the study and participate in as many treatment and evaluation sessions as possible, they will be offered different dates of evaluation. The data collected from participants who prematurely finish the study will be used for partial data analysis. Interviewers involved in assessment and data collection will be trained centrally in trial requirements, ensuring that they have full knowledge of all measurement scales and know how to correctly administer tests. All interviewers will also receive training in the outcome measures used during the trial and will comply with the same administration criteria and standards for every scale and measurement used. Interviewers will have access to video guidelines for the correct administration and scoring of all tests used during the study. During training, interviewers will learn how to administer each test used in the study following the video guidelines. Subsequently, to ensure correct scoring, interviewers will have to score a tested person featured in the video with a requirement of inter-rater reliability of *κ* = 0.80 (between the interviewer in the training and the interviewer from the video). Study coordinators will be responsible for correct data collection and administration of all tests by interviewers.

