### Sample size

Maximal sample size for the study was set at 400 participants with dementia and MCI. We considered a 15% dropout by participants during the 12 months of interventions and 12 months of follow-up. Therefore, the final sample size for the study is likely to be 340 participants.

Considering that the standard deviation of the selected population in the selected variables of the study was unknown and the population size was undetermined, we opted for a calculation of the sample size for an infinite population with the maximal level of variability of the dependent variables of the study (*p* = *q* = .5). If the population scattering parameters are unknown, this calculation allows for a more conservative sample size, meaning the biggest sample size [30].

The calculation was executed using the following equation (α = .05):$$ n=\frac{Z_{\raisebox{1ex}{$\propto $}\!\left/ \!\raisebox{-1ex}{$2$}\right.}^2\ast {0.5}^2}{e^2}, $$

where 0.52 is a maximal variability (*p* * (1 − *p*)), *Z*_∞/2_ corresponds to scores in the percentile *α*/2 (.025) of a normal distribution, and *e* corresponds to the error acquired for the desired sample size, with a result of *e* = 5.3% for a sample size of 340 participants.

On the other hand, based on the Friedman table for determining effect size [31], for the primary outcome measure ADASCog to achieve 80% power (alpha 0.05) on a sample of 340 participants we are looking for an approximate effect size of 0.30, which is similar to a separate study protocol on cognitive rehabilitation in PwD [9].

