### Analysis

Statistical analysis will be conducted using programme IBM SPSS v.23. A descriptive analysis of demographic and personal data will be conducted and results will be compared between all groups. Firstly, an analysis of normality and homogeneity of the data will be conducted. For normally distributed data, the repeated measures analysis of variance (ANOVA) will be used to examine the hypotheses in inter-subject and intra-subject analysis as well as in their interaction. This will be applied to all outcome measures in a comparative analysis of the data collected at from baseline, after 4 months and 12 months of the treatment. In case of non-homogeneous data, non-parametric methods will be used for analysis (Mann–Whitney *U* test, Kruskal-Wallis analysis of variance, Wilcoxon signed-rank test, calculation of Spearman’s correlation coefficient, etc.). Bonferroni/Dunnet corrections will be applied during post-hoc analysis if needed. The possible effects of randomisation bias will be analysed using linear-mixed models including within-group and between-group factors. The significance level will be set at *α* = .05.

Effect sizes and their respective standard errors (SE) and confidence intervals will be estimated as Standardised Mean Change Index (dMR) for within-group comparisons, and as Standardised Mean Index difference (dC) for between-group comparisons, and corrected for small sample sizes [54]:

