## Discussion

We will conduct a RCT with a long-term cognitive rehabilitation intervention and follow-up. This innovative RCT aims to determine the influence of a long-term, computerised, cognitive rehabilitation programme on people with MCI and PwD in comparison to psychosocial stimulation and TAU. The preliminary usability study will focus on ensuring that this type of treatment is more convenient and beneficial for older people, as well as for healthcare professionals.

Limitations of the study are related to the long duration of the treatment along with the 1 year follow-up. Therefore, we expect a large number of participants to drop out due to loss of interest, medical reasons or worsening of a related health condition, changes in life situation, etc. This potential dropout rate has been considered in the sample size calculation to ensure the success of the trial. We also foresee the potential for interviewers and staff to drop out during the study. In this case, every new member of staff recruited will be informed about the study and every new interviewer will undergo the same training in evaluation tools as those recruited at the start of the study.

For ethical and practical reasons, participants in this study will not be blinded to the intervention condition. Huntley et al. [55] recommend conducting single-blinded psychosocial intervention RCTs to minimise other factors, such as socialisation, when using the TAU control group (e.g. patient blinded and assessor blinded, but not therapist blinded). However, this is difficult to apply in practice due to ethical reasons. Therefore, we are conducting a single-blinded RCT with four parallel groups. In this study, all interviewers will be blinded to participants’ treatment allocation. Study coordinators who will manage and adjust the GRADIOR treatments of all participants will do so only based on data obtained from the programme and manage this under a participant’s code (Fig. 1 and Additional file 1).

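### The repeated-measures ANOVA over baseline, 4 and 12 months leaves out anyone missing a visit, so the ADASCog comparison may be biased by dropout; the mixed model already named should be primary

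*Protocol article*

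**What the plan says.** Under Analysis, for normally distributed data, "the repeated measures analysis of variance (ANOVA) will be used to examine the hypotheses in inter-subject and intra-subject analysis". The same section applies this to every outcome measure at baseline, 4 months and 12 months, so it covers ADASCog, the primary outcome. If the data are not homogeneous, rank-based tests take over. Linear mixed models appear in the section with one stated purpose: "The possible effects of randomisation bias will be analysed using linear-mixed models including within-group and between-group factors".

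Treatment adherence deals with early leavers in one sentence: "The data collected from participants who prematurely finish the study will be used for partial data analysis". It does not say what that analysis is or how it relates to the ANOVA.

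On the amount of dropout, Sample size says: "We considered a 15% dropout by participants during the 12 months of interventions and 12 months of follow-up". On the reasons, the Discussion says: "we expect a large number of participants to drop out due to loss of interest, medical reasons or worsening of a related health condition". The Discussion also states that participants are not blinded.

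**The concern.** A classical repeated-measures ANOVA needs a complete row for each person. A participant who leaves after month 4 is dropped entirely, 4-month score included. So is one who misses month 4 but returns at month 12. The people left are selected after randomisation.

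That matters if leaving is related to cognition and the relation or the rate differs by arm. The protocol makes both plausible. Worsening health is a named reason for leaving, and in MCI or dementia it is likely to go with a worse ADASCog score. The arms ask different things of unblinded participants: regular GRADIOR sessions, weekly hours on ehcoBUTLER, both, or no study sessions and a place on a waiting list. If decliners leave one arm more often than another, that arm's remaining participants look better without any treatment effect.

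**Working it through.** **The plan's own figure.** 400 × (1 − 0.15) = 340, as stated. This is ordinary allowance for dropout. The 15% covers 24 months, while the ANOVA ends at month 12.

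**Who enters the ANOVA.** If the whole 15% were lost by month 12, about 340 of 400 would have all three visits. If a further 5% missed a single visit (assumption), 340 × 0.95 = 323 would remain. The rank-based fallback does not remove the problem. A signed-rank test needs both visits of the pair, and a comparison at month 12 needs the month-12 score. A between-arm rank test at month 4 would, however, use everyone seen then.

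**Size of a possible bias.** The documents give neither dropout by arm nor correlations between visits, so everything below is assumed.

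*Simulation inputs:* 100 per arm; no true effect; score SD 1 at each visit; correlations 0.8 (baseline and month 4), 0.8 (months 4 and 12) and 0.7 (baseline and month 12); dropout after month 4 depending on the change from baseline to month 4 (logistic slope 1 to 1.5 per SD of change); 4,000 replicates. The completer estimate is the difference between arms in change from baseline to month 12. The likelihood estimate uses every observed visit.

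Overall dropout across three active arms and TAU:
- 18% v 6%: (3 × 18 + 6)/4 = 15%
- 9% v 3%: (3 × 9 + 3)/4 = 7.5%, half the planned loss

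| Dropout by month 12, active v TAU | Completer bias (SD) | False-positive rate |
|---|---|---|
| 15% v 15%, same mechanism | 0.00 | about 5% |
| 18% v 6% | 0.05 to 0.06 | about 7% to 9% |
| 9% v 3% | 0.03 to 0.04 | about 6% |
| 6% v 18% (reversed) | −0.05 to −0.07 | similar to 18% v 6% |

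A positive sign favours the active arm. Against the effect size of 0.30 in Sample size, 0.05 to 0.06 is 0.05/0.30 = 17% to 0.06/0.30 = 20%. With equal dropout the only cost is precision: SE 0.122 v 0.119, a ratio of 1.025, or about 3%.

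**Check by formula.** Let a fraction d leave because a latent variable, correlated r with the analysed outcome, exceeds t = Φ⁻¹(1 − d). The completer mean then shifts by r × φ(t)/Φ(t).
- d = 0.18: t = 0.915, φ/Φ = 0.262/0.82 = 0.320
- d = 0.06: t = 1.555, φ/Φ = 0.119/0.94 = 0.127
- Difference 0.193; times r = 0.2, 0.3, 0.5 gives 0.04, 0.06, 0.10 SD of the analysed quantity

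This is the same order as the simulation.

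**What the mixed model repairs.** When dropout depended only on the observed 4-month change, the likelihood estimate had bias of about 0.00. That follows from the assumption. When dropout was made to depend on the unseen 12-month change (18% v 6%), completer bias was 0.08 to 0.10 SD and the likelihood estimate still carried 0.05 to 0.06 SD.

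**The case against.** The strongest reply is that the article does not say early leavers are excluded. It says their data will be used, and a partial analysis could mean an analysis of whatever visits exist. The analysis population and missing-data rules are also commonly left to a fuller document. This stands in part. A reader might infer that leavers' data are set aside or discarded, but the text does not say so. It remains that the ANOVA, as the named method, cannot take incomplete rows, whatever the partial analysis turns out to be. The point concerns a stated method, not a missing detail.

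Four other stronger readings are tempting and are not supported:
- That the expected 340 shows who will be analysed. A trial with a mixed model as primary analysis would plan its numbers in the same way.
- That the bias favours the active arms. The Discussion lists reasons for leaving but says nothing about arms. TAU participants face the same five assessments, with a cognitive battery of 106 minutes, and receive neither programme during the trial; the waiting-list offer pulls the other way.
- That the false-positive rate could reach about 15%. That needs 30% v 10%, or (3 × 30 + 10)/4 = 25% overall, well above the planned 15%.
- That a mixed model has no bearing on randomisation bias. Allocation is by simple randomisation, and a covariate-adjusted mixed model can address chance imbalance.

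**Conclusion.** The concern holds in a limited form. The named ANOVA covers only participants with complete visits, in a trial that itself expects many to leave, some for health reasons. Bias in either direction is possible, but its size and sign cannot be derived from the document. Under assumed unequal dropout within the planned total it is about 0.05 to 0.06 SD, with a false-positive rate of about 7% to 9%. It is about 0.03 to 0.04 SD if half the loss comes after month 12. It is nil, with about a 3% larger SE, if dropout is equal and has the same mechanism in each arm. A mixed model removes the bias only as far as dropout depends on observed scores. This should be fixed, because a better method already stands in the same section; the document does not show that the primary result is invalid.

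**What to change.** - **Analysis:** make the linear mixed model the primary ADASCog analysis. Include all randomised participants in their allocated arm, every available visit including those of early leavers, and arm by visit. Read GRA v TAU and COM v TAU from it.
- **Treatment adherence:** replace the sentence on partial analysis with a statement that early leavers' visits enter this model.
- **Sensitivity analyses:** keep the complete-case ANOVA as one. Add one for dropout that depends on unobserved scores, for example by assigning worse outcomes to those who left because of worsening health. The voluntary exit questionnaire can supply the reason where it was answered.

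The cost is protocol wording. Linear mixed models are already planned in the same analysis, and no new data or visits are needed. The change should be made before outcome data are seen by arm, since a later switch would look driven by the results.
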